## Abstract

**Background:**

In the United Kingdom (UK), there is an extensive market for the class 'A' drug heroin. Many heroin users spend time in prison. People addicted to heroin often require prescribed medication when attempting to cease their drug use. The most commonly used detoxification agents in UK prisons are buprenorphine, dihydrocodeine and methadone. However, national guidelines do not state a detoxification drug of choice. Indeed, there is a paucity of research evaluating the most effective treatment for opiate detoxification in prisons. This study seeks to address the paucity by evaluating routinely used interventions amongst drug using prisoners within UK prisons.

**Methods/Design:**

The Leeds Evaluation of Efficacy of Detoxification Study (LEEDS) Prisons Pilot Study will use randomised controlled trial methodology to compare the open use of buprenorphine and dihydrocodeine for opiate detoxification, given in the context of routine care, within HMP Leeds. Prisoners who are eligible and give informed consent will be entered into the trial. The primary outcome measure will be abstinence status at five days post detoxification, as determined by a urine test. Secondary outcomes during the detoxification and then at one, three and six months post detoxification will be recorded.

## Background

In the United Kingdom (U.K), there is an extensive market for the sale of heroin, an illicit class 'A' drug. Precise figures of how many people use and are dependent on heroin are difficult to establish as there has never been a national prevalence survey [1]. The link between crime and illicit drug use, specifically heroin use, is well recognised. In 2002, 63% of injecting drug users (IDUs) in contact with specialist drugs services in England and Wales reported having ever been in prison or a young offenders' institution [2]. Those addicted to illicit opiates such as heroin require medical help in reducing and stopping their use due to the drug's highly addictive properties.

Neither the current evidence base [1] nor the national guidelines on the clinical management of drug misuse [3] stipulate a 'drug of choice' for rapid opiate detoxification. In the absence of an established evidence base, a wide variety of agents have therefore been used including methadone, dihydrocodeine, buprenorphine, lofexidine and clonidine. Historically within prisons, the most commonly used drug for opiate detoxification has been dihydrocodeine. Anecdotally this was because of a reluctance to prescribe methadone following a small number of methadone related deaths in the prison setting. Dihydrocodeine is attractive to clinicians as it has a shorter half-life than methadone, and seems equally acceptable to users. However, there has been a move away from prescribing dihydrocodeine due to its potential for diversion by prisoners into the prison shadow economy. Increasingly, buprenorphine is now being prescribed and recent policy supports methadone prescribing [4]. Buprenorphine – in the form of sub-lingual tablets – is relatively new for the purpose of opiate detoxification in the UK, especially within the prison estate. It has the potential advantage of having a good safety profile, better retention in treatment and lower withdrawal severity when compared to methadone, lofexidine or clonidine [5-8]. Her Majesty's Prison (HMP) Leeds saw a 42% increase in buprenorphine prescribing between April 2002 and January 2004. Buprenorphine is increasingly being prescribed in the community [9].

There appears to be a paucity of clinical trials conducted in the UK prison setting which have evaluated medication for opiate detoxification. Whilst one study evaluated the withdrawal severity of methadone and lofexidine [10], the rates of completion were not sufficient to detect a statistically significant difference between the two medications. One study has compared sublingual buprenorphine with dihydrocodeine for postoperative pain, outside of the prison setting [11]. In 2004, the Leeds Evaluation of Efficacy of Detoxification Study (LEEDS) team conducted the first randomised controlled trial (RCT) to compare buprenorphine and dihydrocodeine for opiate detoxification in the community [12]. The results have recently been submitted for publication. The LEEDS trial has since expanded to evaluate the open use of buprenorphine versus dihydrocodeine in the prison primary healthcare setting.

## Methods

### Design

LEEDS is a pragmatic open label randomised controlled trial.

Randomisation will be random block size, which will be administered centrally in the Academic Department of Psychiatry and Behavioural Sciences, University of Leeds. Opaque consecutively numbered envelopes will be prepared. If a prisoner is both eligible and agreeable the next envelope will be opened and the intervention allocated.

Confounding variables i.e. doctor participant relationships, drugs worker participant relationships will all be controlled for by randomisation. Some confounding variables cannot be randomised. These include the inherent difference in the two detoxification programmes, i.e. the daily supervised consumption of buprenorphine.

### Setting and recruitment

The study will take place in prison primary healthcare at HMP Leeds, West Yorkshire, England. HMP Leeds is a category B local prison, which accepts all adult male prisoners aged 21 and over from West Yorkshire. Participants will be recruited from the medical reception area on first arrival into the prison, where prisoners are routinely offered at detoxification regime.

LEEDS is intended to complement rather than compete with research taking place in a community primary or secondary care setting. Much of the current evidence base for pharmacological treatment of drug use comes from studies that have taken place in an inpatient or residential setting. There is an urgent need to verify whether such research is applicable to the prison primary healthcare environment. The ethos of the study will be a collaborative project between prison primary healthcare, primary care and the secondary care academic departments and service providers.

### Sample size

Currently no randomised controlled trials relevant to these comparisons have been undertaken in the prison setting. However, from the results of our community study comparing these agents we estimate that with a sample size of 120 we will have a finding of clinical and statistical significance. Power calculations were undertaken using Sample Power 1.20 developed by SPSS Inc., comparing two groups (60 individuals in each) and for α = 0.05 (two-sided). The power calculations are shown below in Table 1.

**Table 1 T1:** Power calculations for sample of 120Difference between groups

	**Power**	**Difference between groups**	**Power**
70% × 60%	21%	40% × 30%	21%
70% × 50%	61%	40% × 20%	67%
70% × 45%	80%	40% × 15%	88%
70% × 40%	92%		
60% × 50%	20%	30% × 20%	24%
60% × 40%	59%	30% × 15%	50%
60% × 35%	79%	30% × 10%	79%
60% × 30%	92%		
50% × 40%	20%	20% × 15%	11%
50% × 30%	61%	20% × 10%	33%
50% × 25%	82%	20% × 5%	70%

### Eligibility

#### Inclusion criteria

1. Male or female

2. 18 – 65 years old

3. Using illicit opiates as confirmed by a urine test taken at first assessment.

4. Expressing a wish to detoxify through the standard monitored process and remain abstinent from opiates.

5. Willing to give informed consent after receiving the participant information booklet

6. Remaining in custody for longer than 28 days

#### Exclusion criteria

1. Contraindications to methadone or buprenorphine

2. Co-existing acute medical conditions requiring emergency admission for hospital care so precluding detoxification in the prison setting

3. Currently undergoing detoxification from other addictive drugs whereby concurrent detoxification from opiates would not be clinically indicated

4. Previously been randomised into this trial

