### Interventions

The treatment option will be concealed from both participant and clinician at time of assessment. Both parties will remain blind to the selected treatment option until the envelope is opened.

1. Dihydrocodeine, given openly, in the context of the standard prison doctor and drugs worker support.

2. Buprenorphine, given openly, in the context of the standard prison doctor and drugs worker support.

The reducing regimen of both dihydrocodeine and buprenorphine (over less than 16 days) will be at the discretion of the prescribing doctor. However, the dose should not exceed this standard regime (Table 2 and Table 3).

**Table 2 T2:** Buprenorphine detoxification

**Day**	**Dose (mg)**
1	6
2	8
3	8
4	6
5	6
6	4
7	3.6
8	3.2
9	2.8
10	2.4
11	2.0
12	1.6
13	1.2
14	0.8
15	0.4

**Table 3 T3:** Dihydrocodeine detoxification

Day	Morning	Evening
1	XXXX	2 × 120 mg
2	2 × 120 mg	2 × 120 mg
3	1 × 120 mg 1 × 90 mg	1 × 120 mg 1 × 90 mg
4	1 × 120 mg 1 × 90 mg	1 × 120 mg 1 × 90 mg
5	2 × 90 mg	2 × 90 mg
6	2 × 90 mg	2 × 90 mg
7	1 × 90 mg 1 × 60 mg	1 × 90 mg 1 × 60 mg
8	1 × 90 mg 1 × 60 mg	1 × 90 mg 1 × 60 mg
9	2 × 60 mg	2 × 60 mg
10	2 × 60 mg	2 × 60 mg
11	1 × 60 mg	2 × 60 mg
12	1 × 60 mg	2 × 60 mg
13	1 × 60 mg	1 × 60 mg
14	1 × 60 mg	1 × 60 mg
15	XXXX	1 × 60 mg

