### Consent

Consent for the participant to enter the trial will be gained at first presentation to the prison doctor once eligibility criteria have been confirmed. Consent will be obtained in the form of written consent after the participant has made an informed decision. Information will be provided to the participant using an information leaflet documenting the aims, objectives and necessity of the study, which has been approved by the research ethics committee (MREC Wales).

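### The contraindication exclusion names methadone, which neither arm gives, and omits dihydrocodeine, which half of the participants are to receive

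*Protocol article*

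**What the plan says.** The abstract (Methods/Design) states that the trial will "compare the open use of buprenorphine and dihydrocodeine for opiate detoxification". The Interventions section lists the same pair. Its first arm is "Dihydrocodeine, given openly, in the context of the standard prison doctor and drugs worker support" and its second is buprenorphine under the same conditions. Each drug has its own dosing table (Tables 2 and 3).

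Exclusion criterion 1 reads "Contraindications to methadone or buprenorphine".

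The order of steps is also stated. Consent is "gained at first presentation to the prison doctor once eligibility criteria have been confirmed" (Consent). Then, "If a prisoner is both eligible and agreeable the next envelope will be opened and the intervention allocated" (Design). On what the doctor may vary, Interventions says "The reducing regimen of both dihydrocodeine and buprenorphine (over less than 16 days) will be at the discretion of the prescribing doctor", within the ceiling set by the dosing tables.

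**The concern.** A contraindication exclusion should ensure that every entrant can safely take whichever treatment the envelope contains. Here one of the two drugs is missing from the check, and a drug that the trial does not give stands in its place. The criterion can therefore give the wrong decision in both directions.

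- **Wrongly admitted:** a prisoner with a contraindication to dihydrocodeine but to neither methadone nor buprenorphine.
- **Wrongly excluded:** a prisoner with a contraindication to methadone but to neither study drug.

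The first error bears on safety. Clinician and participant do not know the allocation until the envelope is opened, so fitness for both drugs has to be settled beforehand. If the prescriber notices the problem only when writing the dihydrocodeine prescription, the participant has already been randomised.

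There is a possible further effect on the primary outcome. Someone who does not finish the course is scored as opiate-positive, so a late discovery could count as a failure in one arm. The article does not describe withdrawal or switching for a contraindication, so this route is possible but not established.

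**Working it through.** The claim is settled mainly by setting the sections side by side.

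| Place in the article | Buprenorphine | Dihydrocodeine | Methadone |
|---|---|---|---|
| Abstract, Methods/Design (comparison) | yes | yes | no |
| Background (aim of the prison trial) | yes | yes | no |
| Interventions (arms, Tables 2 and 3) | yes | yes | no |
| Analysis (Table 4 rows) | yes | yes | no |
| Exclusion criterion 1 | yes | **no** | **yes** |

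Methadone otherwise appears only in the abstract's and the main Background, as an agent used in practice and in earlier research.

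**Does another criterion cover the gap?** Exclusion 2 concerns acute illness needing emergency hospital admission. Exclusion 3 concerns concurrent detoxification from other addictive drugs. Exclusion 4 concerns earlier randomisation into this trial. None of the six inclusion criteria mentions contraindications. So no.

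**Does another step cover it before allocation?** The doctor completes the outside of the envelope first, but that records identifiers, severity of addiction and expected prognosis (Data collection), not fitness for each drug. The prescriber's stated discretion concerns how the dose is reduced, not whether the allocated drug is given. So no.

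**Share of participants concerned.** The Sample size section plans two groups of 60, so 60 / 120 = 0.50 are allocated to dihydrocodeine.

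**Planned power.** The Table 1 figures were recomputed only to confirm that the correction leaves them alone. With n = 60 per group, two-sided alpha 0.05 and p̄ the mean of p1 and p2:

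power = Φ{ [ |p1 − p2| − 1.96 √(2p̄(1 − p̄)/n) ] / √( [p1(1 − p1) + p2(1 − p2)]/n ) }

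For 70% against 45%: the null standard error is √(2 × 0.575 × 0.425 / 60) = 0.0903, and the alternative one is √((0.21 + 0.2475) / 60) = 0.0873. Then (0.25 − 1.96 × 0.0903) / 0.0873 ≈ 0.84, which gives 79.9% against the stated 80%. All 20 entries reproduce to within one percentage point. None depends on which contraindications are screened.

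**Effect on the primary outcome, hypothetical only.** Suppose one dihydrocodeine participant is scored a failure because of a contraindication and would otherwise have been abstinent with probability p. The expected drop in that arm's observed success is p / 60. Taking the success rates in Table 1 (5% to 70%) as an assumed range for p:

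- p = 0.05: 0.05 / 60 = 0.08 percentage points
- p = 0.50: 0.50 / 60 = 0.83 points
- p = 0.70: 0.70 / 60 = 1.17 points
- ceiling, p = 1: 1 / 60 = 1.67 points

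The number of such participants is not given, so no total can be computed.

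**The case against.** The strongest reply accepts the mismatch and disputes how much it matters. This looks like a one-word drafting slip. A prison doctor sees every candidate before the envelope is opened, both drugs are given in routine care, and the Background describes dihydrocodeine as historically the usual detoxification agent in prisons. Such a doctor may well screen for it whatever the criterion says. The contraindications to the three opioids may also overlap so far that hardly anyone is misclassified. In a pragmatic trial, being unable to take the allocated drug can be seen as a real failure of that strategy and not as bias. Finally, 50% is the allocation ratio, not the proportion at risk.

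Much of this stands as a limit on size. Harm to any participant is not shown, the overlap is unknown, the primary-outcome route is unproven, and the p/60 figures do not measure the error. Removing methadone is also less urgent than adding dihydrocodeine, because the methadone wording only costs eligible participants.

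None of it makes the criterion right. The article neither states nor relies on overlap. A doctor's vigilance is not part of the eligibility rule, and the rule as written does not prompt it before allocation. Nor does condensation into a journal article explain it: the criterion is present and names the wrong drug.

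**Conclusion.** The concern holds: exclusion 1 contradicts the trial's own treatment arms. It should be corrected before anyone is randomised under it, on grounds of participant safety and correct eligibility.

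The contraindication check does not name the drug planned for 60 of 120 participants. The number of prisoners wrongly admitted or wrongly excluded, and any effect on the abstinence comparison, cannot be determined from the article. The conclusion needs no assumption about those numbers. It rests only on applying the criterion as written and on the stated sequence of eligibility, consent and envelope. Whether the full protocol carries the same wording cannot be seen here.

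**What to change.** Reword exclusion 1 as *Contraindications to dihydrocodeine or buprenorphine*. Remove methadone unless the clinical lead gives a reason to keep it; if it stays, list it in addition to the two study drugs. Both possible allocations are then screened before the envelope is opened.

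The cost is a one-line amendment and a corrected eligibility checklist, or only a correction to the article if the full protocol already has the right wording. The net effect on the number eligible is unknown: adding dihydrocodeine may exclude some prisoners, and removing methadone may admit others.

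A minor point could be tidied in the same edit. The inclusion criteria say "Male or female" and 18 to 65 years, while the only site "accepts all adult male prisoners aged 21 and over from West Yorkshire". Male, 21 to 65, would match the site and keep the upper limit. The mismatch admits nobody wrongly, because the site already limits who arrives.

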### Interventions

The treatment option will be concealed from both participant and clinician at time of assessment. Both parties will remain blind to the selected treatment option until the envelope is opened.

1. Dihydrocodeine, given openly, in the context of the standard prison doctor and drugs worker support.

2. Buprenorphine, given openly, in the context of the standard prison doctor and drugs worker support.

The reducing regimen of both dihydrocodeine and buprenorphine (over less than 16 days) will be at the discretion of the prescribing doctor. However, the dose should not exceed this standard regime (Table 2 and Table 3).

**Table 2 T2:** Buprenorphine detoxification

**Day**	**Dose (mg)**
1	6
2	8
3	8
4	6
5	6
6	4
7	3.6
8	3.2
9	2.8
10	2.4
11	2.0
12	1.6
13	1.2
14	0.8
15	0.4

**Table 3 T3:** Dihydrocodeine detoxification

Day	Morning	Evening
1	XXXX	2 × 120 mg
2	2 × 120 mg	2 × 120 mg
3	1 × 120 mg 1 × 90 mg	1 × 120 mg 1 × 90 mg
4	1 × 120 mg 1 × 90 mg	1 × 120 mg 1 × 90 mg
5	2 × 90 mg	2 × 90 mg
6	2 × 90 mg	2 × 90 mg
7	1 × 90 mg 1 × 60 mg	1 × 90 mg 1 × 60 mg
8	1 × 90 mg 1 × 60 mg	1 × 90 mg 1 × 60 mg
9	2 × 60 mg	2 × 60 mg
10	2 × 60 mg	2 × 60 mg
11	1 × 60 mg	2 × 60 mg
12	1 × 60 mg	2 × 60 mg
13	1 × 60 mg	1 × 60 mg
14	1 × 60 mg	1 × 60 mg
15	XXXX	1 × 60 mg

### Outcomes

#### Primary outcome

Abstinence from street opiates at five days post detox as indicated by urine test. Should the person not finish the course of detoxification or refuse to give urine then this will be considered as a positive urine test for opiates.

#### Secondary outcomes

##### During the period of detoxification

###### Adverse events

Clinicians will record any details of adverse events in the usual way i.e. an entry will be made in the participants' records. Those adverse events clearly resulting in clinically significant distress to study participants or of major concern to clinicians will be recorded. The LEEDS trial co-ordinator will extract data from clinical records, for the period of detoxification, and transcribe these to a database.

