###### Leaving the study early

Perceived reasons for withdrawal will be recorded.

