###### Service utilisation

Contacts with hospitals and Accident and Emergency departments will be noted. For those participants still in the prison estate, use of inpatient prison healthcare will be recorded.

The project team recognise the difficulty in tracking people with drug problems who have subsequently been released from prison across this period.

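### Adverse events are extracted only for the detoxification period, which varies in length and has no stated end for early leavers, so observation time can differ between arms

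*Protocol article*

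**What the plan says.** All references are to the protocol article.

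- **Adverse events** (a secondary outcome listed under the detoxification period): "The LEEDS trial co-ordinator will extract data from clinical records, for the period of detoxification, and transcribe these to a database". There is a severity threshold: "Those adverse events clearly resulting in clinically significant distress to study participants or of major concern to clinicians will be recorded". No calendar length is given, and no end rule for a participant who stops early.
- **Interventions**: "The reducing regimen of both dihydrocodeine and buprenorphine (over less than 16 days) will be at the discretion of the prescribing doctor". Treatment is open, and the standard schedules in Tables 2 and 3 run to day 15.
- **Primary outcome**: urine is tested five days after detoxification. Non-completion is foreseen and scored as an opiate-positive result: "Should the person not finish the course of detoxification or refuse to give urine then this will be considered as a positive urine test for" (…).
- **Leaving the study early**: "Perceived reasons for withdrawal will be recorded". Nothing is said about collecting adverse events after that.
- **Inappropriate use of prescribed medication**: intentional overdose is given as an example, again under the detoxification period.
- **Service utilisation** at one, three and six months: "Contacts with hospitals and Accident and Emergency departments will be noted". Use of inpatient prison healthcare is also recorded for those still in the prison estate. The section concedes that people are hard to trace after release.

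**The concern.** The safety window is tied to treatment. Its length is chosen by someone who knows the drug, and on the natural reading it is cut short when a participant stops. Two participants at equal daily risk can then be watched for different lengths of time, and if course length or dropout differs by drug, so does average observation time per arm. The Analysis section describes simple participant-count tables and mentions no time at risk, so nothing stated would correct for this.

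Separately, efficacy is judged five days after the course ends, a point that adverse-event extraction does not reach for a full 15-day course. Any event in the days just after stopping is picked up only if it led to a recorded service contact. Deaths are not listed as an outcome anywhere, and an overdose after detoxification without such a contact has no place to be recorded.

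The Discussion expects the results to influence prescribing policy at HMP Leeds and possibly nationally, so the safety comparison will be read alongside the abstinence result.

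**Working it through.** **The plan's own figures.** The article gives no figure for adverse events, dropout or time observed, so there is none to reproduce on this point. The only computed figures are the powers in Table 1 (60 per arm, two-sided 0.05). All 20 reproduce within 2 points by the pooled-variance normal approximation (70% v 45%: 79.9% against the stated 80%). They do not bear on this question.

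**Step 1: the gap common to both arms.** Full course, 15 days (Tables 2 and 3). Urine test five days later, day 20. Not extracted: 5 / 20 = 25% of the time to the primary endpoint. This needs no assumption about dropout. It applies equally to full-course participants in both arms, so it is a gap in coverage and not a between-arm bias.

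**Step 2: observation time if the window closes at leaving.** Assumed: share leaving early *d*, all on day *L*, otherwise a 15-day course.

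Mean days = (1 − d) × 15 + d × L

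- d = 20%, L = 5: 0.8 × 15 + 0.2 × 5 = 13.0 days
- d = 40%, L = 5: 0.6 × 15 + 0.4 × 5 = 11.0 days
- d = 60%, L = 5: 0.4 × 15 + 0.6 × 5 = 9.0 days

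**Step 3: observed risk when true risk is equal.** Assumed: true 15-day risk *R* in both arms and a constant hazard λ = −ln(1 − R) / 15.

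Observed risk = (1 − d) × R + d × (1 − exp(−λL))

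With R = 20%, λ = 0.2231 / 15 = 0.01488, and for L = 5, 1 − exp(−0.0744) = 0.0717.

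- d = 20%: 0.8 × 0.20 + 0.2 × 0.0717 = 17.4%
- d = 40%: 0.6 × 0.20 + 0.4 × 0.0717 = 14.9%; ratio to the 20% arm 0.85
- d = 60%: 0.4 × 0.20 + 0.6 × 0.0717 = 12.3%; ratio to the 20% arm 0.71

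With 60 per arm, 17.4% v 14.9% is about 10.4 v 8.9 participants, a difference of about 1.5.

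**Step 4: range at a constant hazard** (R from 10% to 30%, leaving on day 3, 5 or 7).

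| Dropout | Observed risk ratio (higher-dropout arm / other) |
|---|---|
| 20% v 40% | 0.81 to 0.89 |
| 30% v 50% | 0.79 to 0.89 |
| 20% v 60% | 0.62 to 0.78 |

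**Step 5: events concentrated early.** If a share *s* of events falls before the day of leaving:

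Ratio = (1 − d₂(1 − s)) / (1 − d₁(1 − s))

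- s = 80%: 0.92 / 0.96 = 0.96 (20% v 40%); 0.88 / 0.96 = 0.92 (20% v 60%)
- s = 90%: 0.96 / 0.98 = 0.98 (20% v 40%); 0.94 / 0.98 = 0.96 (20% v 60%)
- s = 100%, or equal dropout with the same leaving day: 1.00

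**Step 6: a common window.** If everyone is observed from randomisation to the same day whether or not treatment continues, equal true risk gives an expected ratio of 1.00 whatever the dropout.

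**The case against.** The case on the other side has real force.

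- **The end of the window is not stated.** A reader might infer that the article closes extraction when a participant leaves. It does not say so. Reading the notes over the standard 15 days for everyone is also possible, and the full protocol or the dummy tables not shown may settle it. This stands as a limit on the claim. It does not remove the problem: the stated rule still depends on a variable period, allows two readings that give different counts, and for a full 15-day course omits the five days after it on either.
- **Direction is not certain.** A reader might infer that an arm tolerated badly and abandoned early must show fewer events. The article does not support that. Events that cause someone to stop happen before stopping, fall inside the window, and may also appear among the reasons for withdrawal. The distortion needs both unequal dropout and events after leaving. This stands.
- **There is later follow-up.** It would be wrong to say that only hospital and Accident and Emergency contacts are noted: prison inpatient care is too, and inclusion criterion 6 requires more than 28 days in custody, so that source should cover days 16 to 20. This stands, as a partial backstop. These contacts are not recorded as adverse events, and deaths, or overdoses without such contact, are not listed.
- **On-treatment windows are a recognised convention**, and events after stopping may reflect resumed illicit use. That is a reason to label events by timing and keep the on-treatment count, not to leave the later ones unextracted.

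**Conclusion.** The point holds as a weakness of a stated rule. Adverse-event extraction follows a treatment period that varies at the discretion of an unblinded prescriber and has no defined end for early leavers. Observation can therefore differ between arms, and for a full 15-day course the last 5 of the 20 days to the primary urine test go unextracted in both.

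The size of any between-arm distortion is unknown, because the article gives no dropout or event rates. On the assumption that the window closes at leaving, the illustrative ratio at equal true risk runs from about 0.62 (20% v 60% leaving on day 3, constant rate, 10% risk) to 1.00 (equal dropout, or all events before leaving). The middle case of 0.85 rests on 20% v 40% leaving on day 5 at a constant rate.

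The documents do not show that the arm with more dropout will look safer, only that it can. The primary outcome is unaffected, since non-completers already count as failures there. The change is worth making because the safety comparison may inform policy and the remedy is cheap.

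**What to change.** In the adverse-events section, replace the detoxification-period limit with one fixed window: extract adverse events, including death and overdose, for every randomised participant from randomisation to day 20 (the 15-day schedule plus five days), whether or not detoxification was completed. Flag each event as on or after treatment, so that the on-treatment count can still be reported. Add that deaths and overdoses will be noted at the one-, three- and six-month checks already planned.

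This changes data collection only and touches no dose or clinical rule. Day 20 lies within the required custody of more than 28 days, and the article already plans to use clinical notes after transfer to another prison. The same co-ordinator already collects the primary outcome and the follow-up data. The cost is a change of wording and slightly more extraction time.
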